### Trial Statistics

#### Power calculation

We propose a non-inferiority trial following the Consolidated Standards of Reporting Trials (CONSORT) statement for such trials[29]. With a one-sided alpha of 0.05 we have 80% power to detect inferiority of 9.5% in the quit rate at four weeks if we enrol 343 in each arm, assuming 50% 4-week abstinence. Therefore the trial sample size shall be N = 700. Analyses will be carried out on an intention-to-treat basis, according to the Russell Standard, where participants lost to follow up are assumed to be smokers [20].

Arguably, differences of 5% at 4 weeks would be worthwhile detecting[50], but a trial would need to enrol 2500 participants for this, which would make it impractical and unlikely to be funded. If the reduction produced abstinence rates not worse than 9.5% less at four weeks, this is probably sufficient for stop smoking services to implement the programme.

#### Analysis

The analysis will compare the proportions stopping smoking, calculating confidence intervals and relative risks and confidence intervals. We will calculate differences in withdrawal scores using regression, controlling for baseline differences, as is standard using the MPSS[51]. We will investigate possible mechanisms of action (NRT dose, satisfaction from smoking, withdrawal, self-efficacy) using mediation analysis within a regression framework. Mediation analysis is outlined in more detail by the RIPL research group at the Arizona State University[52].

In comparing methods of reduction, we have no specified hypotheses. We will compare changes in confidence, stereotypy, and urges to smoke calculating differences in mean changes and confidence intervals for the difference. We will compare the proportion abstinent using point prevalence and prolonged abstinence as in the comparison between reduction and abrupt cessation. The primary analysis of abrupt cessation versus reduction will not be adjusted by method of reduction used.

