### Allocation to trial arms and treatments

#### Randomisation

Participants will be seen at an assessment session, similar to that used by stop smoking services, where participants will be randomised 1:1 to reduction or abrupt cessation in the assessment session. We will use Stata to accomplish stratified randomisation by therapist with blocking within each stratum to ensure balance. The blocks will be randomly ordered blocks of 2, 4, and 6. Each therapist will open sealed numbered envelopes in turn after consent and initial procedures to determine allocation to abrupt cessation or rapid reduction.

Participants in the reduction arm will be offered a choice of ways to reduce and asked to choose the method they feel is right for them. Those without strong preferences will be randomised to one of the three reduction methods. We will use Stata to accomplish stratified randomisation by therapist with blocking within each stratum to ensure balance. The blocks will be randomly ordered blocks of 3 and 6. Each therapist will open sealed numbered envelopes in turn after consent and initial procedures to determine allocation to abrupt cessation or rapid reduction.

It is quite likely that we will see couples, friends, or relatives who want to quit together and attend clinic as a group. In this situation they will be randomised together so they go into the same arm and given the same study number but made identifiable by adding an A or B to the end of their number.

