• Smoking stereotypy is a measure of the degree to which smoking is prompted by cues to smoke[48]. Perhaps reduction might work by disrupting stimulus control and this scale could measure this. Two questions from this scale will be used to measure smoking stereotypy because the other questions in the scale are either forced to change or could not be assessed over a short period.

There are no specific outcomes proposed when comparing methods of reduction. This analysis will focus on the above measures and is exploratory. See Table 3 for a breakdown of which outcomes are to be measured at specific time-points [49].

**Table 3 T3:** Schedule of trial measures

Follow-up	Trial measures
Baseline (wk -2)	Smoking history, demographics, nicotine dependence using Fagerstrom Test for Nicotine Dependence (FTND)[49], urges and withdrawal (MPSS[51]), confidence in quitting, smoking stereotypy[48], cigarette satisfaction[47], future orientation questionnaire, exhaled carbon monoxide (CO), salivary cotinine, Give out diaries.

Pre-quit visit (wk -1)	CO, cotinine, MPSS, confidence, smoking stereotypy, cigarette satisfaction, adverse events. Collect diaries with daily smoking, NRT use, MPSS urge questions. Give out diaries.

Extra pre-quit visit (wk -1a)	**Only applicable if delays quit date by 1 week** CO, MPSS, confidence, smoking stereotypy, cigarette satisfaction, adverse events. Collect diaries with daily smoking, NRT use. Give out diaries.

Extra pre-quit visit (wk -1b)	**Only applicable if delays quit date by 2 weeks** CO, MPSS, confidence, smoking stereotypy, cigarette satisfaction, adverse events. Collect diaries with daily smoking, NRT use. Give out diaries.

Quit day (wk 0)	CO, cotinine, MPSS, confidence, smoking stereotypy, cigarette satisfaction, adverse events. Collect diaries with daily smoking, NRT use, MPSS urge questions. Give out diaries.

One week after quit day (wk +1)	CO, cotinine, MPSS, confidence, cigarette satisfaction if lapsed, adverse events Collect diaries with daily smoking, NRT use, MPSS urge questions

Post-quit visits (wks +2, +3, +4)	Smoking in past week, CO, MPSS, confidence, cigarette satisfaction if lapsed, future orientation questionnaire at week 4, amount NRT used, adverse events

+8 wk visit	Smoking in past 4 weeks, CO, MPSS, cigarette satisfaction if lapsed, confidence, amount NRT used, adverse events

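### Among participants randomised to a reduction method, comparing mean changes in confidence, stereotypy and urges gives up precision that adjusting for the collected baseline values would recover

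*Protocol article*

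**What the plan says.** The Analysis section of the protocol article sets out the comparison of reduction methods as follows: "We will compare changes in confidence, stereotypy, and urges to smoke calculating differences in mean changes and confidence intervals for the difference". It names no baseline covariate.

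The preceding paragraph, on withdrawal, takes another route: "We will calculate differences in withdrawal scores using regression, controlling for baseline differences, as is standard using the MPSS".

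The baseline row of Table 3 (week -2) includes "urges and withdrawal (MPSS[51]), confidence in quitting, smoking stereotypy[48], cigarette satisfaction[47", so each of the three outcomes has a baseline value. Urges belong to the same scale, the MPSS, as the withdrawal scores.

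The comparison has low status by design. The Analysis section says "In comparing methods of reduction, we have no specified hypotheses", and the text before Table 3 adds "This analysis will focus on the above measures and is exploratory".

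Under Randomisation, participants in the reduction arm first choose a method. Only then: "Those without strong preferences will be randomised to one of the three reduction methods".

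**The concern.** A difference in mean changes subtracts the whole baseline value, which fixes the baseline slope at 1. When baseline and follow-up have similar spread and are imperfectly correlated, the best-fitting slope is below 1, and the forced slope adds noise. A method group that starts high by chance will then tend to show a larger fall even if the methods do not differ.

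Confidence intervals are the planned output of this comparison, and the groups are modest: one arm is split three ways, and only some of its members have their method randomised. Width that could be removed with data already collected is a real, though small, loss. The section itself describes baseline control as standard for the MPSS and gives no reason for handling urges differently here.

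**Working it through.** **The plan's own figures.** None is given for the method comparison. The main sample size reproduces. With 50% abstinence in both arms, a 9.5-point margin, one-sided alpha 0.05 and 80% power, n = 2 × 0.25 × (1.645 + 0.842)² / 0.095², which rounds up to 343 per arm. Nothing below affects it.

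**Inputs.**
- Total N = 700, allocated 1:1 (Power calculation; Randomisation), so about 350 in the reduction arm.
- An even three-way split gives 350/3, about 117 per method. This is an assumption. The groups randomised to a method will be smaller, because those who chose a method are not in them.
- Correlation ρ between baseline and follow-up: not in the document, so a range is assumed.
- Equal SDs at baseline and follow-up: assumed, with the SD set to 1.

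**Precision under randomised allocation.** The variance per participant is 2(1−ρ) for a change score and 1−ρ² for baseline-adjusted regression in large samples. The ratio of adjusted to change is (1+ρ)/2. Interval width scales with its square root. The 95% half-width for two methods is 1.96 × √(2 × variance / n), with n = 350/3.

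| ρ | Change variance | Adjusted variance | Ratio | Interval narrower by | Half-width, change vs adjusted (SD) |
|---|---|---|---|---|---|
| 0.3 | 1.40 | 0.91 | 0.65 | 19% | 0.304 vs 0.245 |
| 0.5 | 1.00 | 0.75 | 0.75 | 13% | 0.257 vs 0.222 |
| 0.7 | 0.60 | 0.51 | 0.85 | 8% | 0.199 vs 0.183 |
| 0.9 | 0.20 | 0.19 | 0.95 | 3% | 0.115 vs 0.112 |

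A simulation with 117 per group and 4000 replicates gave ratios of 0.64, 0.75 and 0.84 at ρ = 0.3, 0.5 and 0.7. In smaller groups both intervals widen, but the ratio stays about the same.

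**Unequal SDs.** The excess variance of the change score is (SD0 − ρ × SD1)², where SD0 is the baseline SD and SD1 the follow-up SD. It is never negative, and it is zero when the baseline slope ρ × SD1/SD0 equals 1.

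**Chance imbalance.** If one randomised group starts 0.2 SD higher and the methods do not differ, the expected difference in change is −(1−ρ) × 0.2, or −0.14, −0.10 and −0.06 SD at ρ = 0.3, 0.5 and 0.7. This is not a second loss on top of the table. The change-score variance splits as 2(1−ρ) = (1−ρ²) + (1−ρ)², and the last term is the contribution of baseline imbalance. At ρ = 0.5 that is 1.00 = 0.75 + 0.25. Over repeated randomisations the shift averages to zero.

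**Self-selected groups.** Suppose participants who chose different methods differ by a stable 0.3 SD and the methods have no effect. In simulation the change score then gave a difference of about 0.00. Baseline adjustment gave 0.15 SD at reliability 0.5 and 0.09 SD at reliability 0.7, in line with 0.3 × (1 − reliability). In that setting the change score does better.

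**Cost of restricting to the randomised.** If a fraction f of the arm is randomised to a method, adjusted analysis of that subset alone has ((1+ρ)/2)/f of the variance of the whole-arm change score. It is more precise only if f exceeds 0.65, 0.75 or 0.85 at ρ = 0.3, 0.5 or 0.7. The document does not give f.

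**The case against.** The strongest case against has five parts.

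- **Nothing rests on this comparison.** It is exploratory, with no hypothesis, test, power claim or decision rule. This stands. A reader might infer that the trial would lose power or favour the wrong method. The document plans no test here and nowhere says that a method will be selected from these results.
- **Method is mostly a matter of choice.** A reader might infer that baseline adjustment should replace mean changes throughout the reduction arm. The self-selection result does not support that: adjustment does not remove self-selection, and either analysis can be defended there. The point therefore covers only those randomised to a method.
- **Chance imbalance is not bias.** This stands. A reader might infer that regression to the mean distorts the comparison systematically. Under randomisation it does not, and the change-score interval already includes that variability. A gap as large as 0.3 SD would also be unusual at 117 per group: the standard error is √(2/117) = 0.13 SD, so the gap is about 2.3 standard errors. Smaller groups make it likelier.
- **Two treatments of the MPSS are not a contradiction.** This also stands. One sentence concerns withdrawal between randomised arms, the other an exploratory comparison within one arm. The contrast shows only that the baseline-adjusted method is already in use in this plan.
- **The wording does not exclude a covariate, and a condensed article leaves covariates to the analysis plan.** In part. Regressing change on method and baseline gives the same method coefficient as regressing follow-up on them, so if that is intended, saying so is enough. But the article does state an estimator, and as written it is a difference in mean changes.

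**Conclusion.** The point holds as a minor refinement. Among participants whose method was randomised, baseline-adjusted regression is unbiased and, in large samples, at least as precise as a change score on the same people. With equal SDs and an assumed ρ of 0.3 to 0.7, intervals would be about 19% to 8% narrower. At ρ = 0.9 the gain is only about 3%. The size depends on ρ, which the document does not give, and the absolute widths depend on how many participants are randomised to a method, which is unknown in advance. For the reduction arm as a whole, the document gives no basis for calling the change score wrong. The abstinence comparison, the 9.5-point margin and N = 700 are unaffected.

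**What to change.** In the Analysis section, add that for participants randomised to a reduction method, each of confidence, stereotypy and urges will be analysed by linear regression of the follow-up score on method and the baseline value of the same measure. Report adjusted mean differences with confidence intervals.

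Keep the comparison of all participants in the reduction arm as a separate, descriptive result, presented by chosen versus randomised method. The adjusted analysis should stand beside it and not replace it, because restricting everything to the randomised subset could lose more precision than adjustment gains.

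The cost is a sentence or two of wording and one extra set of exploratory estimates on a subset of unknown size. No new data, visits or participants are needed. Participants without a baseline score need a simple rule, but they have no change score under the present wording either.

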#### Trial schedule

With two fulltime nurses who will also act as trial co-ordinators and liaise with practices, and do follow ups, and the support of a PhD student, we can see the 700 participants in 24 months (bearing in mind that clinical contacts span 10 weeks).

#### Definition of end of trial

End of trial is defined as the final 6 month patient follow-up measuring carbon monoxide level of the last participant undergoing the trial.

### Safety Reporting

#### Assessment of safety

Potential participants' safety will be ensured by screening for eligibility using a structured form completed by the trial nurse. This will record evidence of eligibility and exclusion criteria. In addition, the nurse will take a general medical history to assess for other complicating diseases. Any queries remaining as a result of this process will be resolved by discussion between the trial nurse, chief investigator and the relevant physicians providing routine medical care, usually the participant's general practitioner. Such concerns are unusual but not rare. Typically, they arise from a participant's hazy knowledge or understanding of their past medical history and are usually readily resolved. No blood or further medical testing will be necessary to ensure safety.

NRT has been investigated in several hundred previous clinical trials and is widely prescribed worldwide and subject to safety monitoring, and is replacing a product, nicotine, which the participants are already consuming and will have consumed for many years in cigarettes. Thus, there is every reason to expect that treatment in this trial will be safe. Participants will be warned about the side-effects of NRT and advised not to stop taking the medication without consulting with an NHS professional, preferably the trial team. To this end, all participants will be given a credit card-sized card with the trial team's contact details on that will allow participants to receive advice on medication or to report perceived serious adverse effects and receive advice on medication as required. Participants will record the occurrence of side-effects of medication as specified on the summary of product characteristics for relevant NRT preparations, by completing a checklist. The checklist will be given to the trial nurse and the nurse will enquire about recorded adverse events, so as to determine the severity of any adverse event and ensure that appropriate advice is given for its management (such as rotating the patch site or use of emollients for skin reactions). Minor adverse reactions will be monitored and managed in this way. For each known side effect listed in the summary of product characteristics, the trial nurse will have a definition of clinical severity. For example, a mild skin site reaction to the patch will be defined as burning sensation that does not interfere with normal activities, redness or swelling at the site of application, or mild blistering. Any reaction beyond that will be classified as potentially moderate or severe and will be reported to and discussed with the principal investigator. A decision on stopping therapy will then be made with the participant, attending clinician, principal investigator, and other relevant parties as appropriate. Nicotine has a short half life (2 hours), meaning that the blood concentration will not build up during the course of treatment so that new side-effects are not expected after the first few weeks. In addition, with reactions relating to local use, such as skin discomfort from patches, or bad taste from oral use, either treatment will have been switched or people become accustomed to the side-effects after a short time of using the preparation. At the last meeting (week 8 of the quit attempt), the participant will be advised to phone the contact number to report side-effects that occur after this. The advice given will depend upon the severity of the reported reaction and those with moderate reactions will be invited to an ad hoc consultation.

Participants will also complete a schedule of nicotine overdose symptoms at each visit. On completion of this questionnaire, the schedule will be handed to the nurse and thus any symptoms of overdose will be assessed. In addition, based on her/his enquiry, the nurse will make an assessment of whether the NRT dose is too high or not, and then what action was taken, such as continue with prescribed dose, or direct the participant to use a lower dose, which will be recorded.

The summary of product characteristics for the relevant NRT products contain no warnings about serious adverse reactions except rare allergic reactions, such as angioedema, and cardiac arrhythmias, occurring in less than 1/1000 users. Thus we expect no or very few suspected unexpected serious adverse reactions (SUSARs) in this trial. The long history of use in and outside of trials for NRT means that SUSARs are unlikely. On the reverse of the trial card given the contact number for advice on side-effect management, there will be instructions for the reporting of serious adverse events. Through direct contact from the participant or contact from their attending physician, we expect to become aware of serious adverse events. If any member of the trial team becomes aware, they will inform the PI within 24 hours. The principal investigator will then assess the seriousness, causality, expectedness and severity of the adverse effects. An immediate decision will be made on the interim use of medication for that participant. If an event is judged severe, it will be reported to the trial sponsor, who will report the event to the Research Ethics Committee and Medicines and Healthcare Regulatory Authority. Participants will be asked weekly to report inter-current illnesses and the response recorded. If any of these inter-current illnesses contra-indicates NRT, this will be immediately reported to the principal investigator and a decision made about continued use of the NRT product. The reporting procedures and definitions are presented in Additional file 1.

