### Ethics and Research Governance

The trial will be conducted in compliance with the principles of the Declaration of Helsinki (1996), the principles of ICH-GCP and run in accord with EU Clinical Trials Directive and all of the applicable regulatory requirements. The study protocol and other documentation have been reviewed and approved by the National Research Ethics Committee (08/H0408/213), the Medicines & Healthcare Regulatory Authority, and local NHS Research & Development offices. Any subsequent protocol amendments will be submitted to the Research Ethics Committee for approval, and the other bodies if necessary. We will comply with ICH-GCP Guidelines over the reporting of adverse events, serious adverse events and suspected unexpected serious adverse reactions (SUSARS). In addition we will provide the Research Ethics Committee with progress reports as well as a copy of the Final Study Report.

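### The written trigger for reporting events to the sponsor, ethics committee and regulator is severity, not seriousness, which conflicts with the protocol's own commitment on serious adverse events

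*Protocol article*

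**What the plan says.** The relevant text is in the Protocol article, under Assessment of safety. Serious adverse events are expected to come to light through participants or their physicians, and any team member who learns of one informs the principal investigator within 24 hours. Then: "The principal investigator will then assess the seriousness, causality, expectedness and severity of the adverse effects". The rule for what leaves the trial team follows: "If an event is judged severe, it will be reported to the trial sponsor", which passes it on to the ethics committee and to the medicines regulator.

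Earlier in the same section, severity is an intensity grade. The nurse holds a definition of clinical severity for each known side effect, with the patch as the example: "a mild skin site reaction to the patch will be defined as burning sensation that does not interfere with normal activities", or redness, swelling or mild blistering. Of anything worse, the text says: "Any reaction beyond that will be classified as potentially moderate or severe".

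Under Ethics and Research Governance the article makes a general commitment: "We will comply with ICH-GCP Guidelines over the reporting of adverse events, serious adverse events" and suspected unexpected serious adverse reactions (SUSARs).

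Two further documents are named but not shown. The safety section refers to Additional file 1 for procedures and definitions. The section on withdrawal criteria announces a work instruction covering serious adverse events and SUSARs.

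**The concern.** Seriousness and severity answer different questions. Seriousness is a category of event, and the article itself uses that category for serious adverse events and SUSARs. Severity is how intense the event is. The article keeps the two apart until the step that decides which events reach the sponsor, the ethics committee and the regulator, and there it names severity.

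What is at stake is participant-safety oversight. Staff who follow the published sentence could route an event by its intensity grade and set aside the seriousness, causality and expectedness judgements that they had just been told to obtain. No endpoint, estimate or sample-size figure depends on it.

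**Working it through.** No arithmetic applies, and the article gives no figure for this point. The check is to set the statements side by side.

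1. **Are the two terms distinct in this document?** Yes. "The principal investigator will then assess the seriousness, causality, expectedness and severity of the adverse effects" lists them as separate items in one sentence. If they meant the same thing, one would be redundant.

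2. **What does *severe* mean here?** The only guidance in the article is the skin-reaction example, which runs from mild upward by intensity and interference with normal activities. No seriousness criterion enters it.

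3. **What does the trigger use?** Only *severe*. Seriousness, causality and expectedness are assessed, but none of them appears in the condition for onward reporting.

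4. **What does the commitment cover?** Adverse events, serious adverse events and SUSARs. As its name says, a SUSAR is defined by suspicion of a causal link, unexpectedness and seriousness. Intensity is not among these.

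5. **Where do trigger and commitment part?** Crossing the two attributes gives four cases:

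| Event | Literal trigger | Within the serious-event commitment? |
|---|---|---|
| Serious, severe | Met | Yes |
| Serious, mild or moderate | Not met | Yes |
| Not serious, severe | Met only if the sentence applies outside the serious-event sequence | No |
| Not serious, mild or moderate | Not met | No |

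The second row is the conflict: an event that the governance section promises to report has no stated route beyond the principal investigator. The third row depends on how far the sentence reaches, and the finding does not rest on it.

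**The case against.** The strongest reply is that this is loose wording in a condensed article. The sentences around the trigger are about serious adverse events: "Through direct contact from the participant or contact from their attending physician, we expect to become aware of serious adverse events", then the 24-hour notice, the assessment and the onward report. In that setting *severe* can be read as a slip for *serious*. The paragraph also ends by sending the reader to Additional file 1, and the work instruction may hold the correct rule. This stands in part. It means that nobody can say from the article that reporting would fail. It does not clear the sentence. Deferring to another file excuses detail left out, but here a specific trigger is stated and it names the wrong attribute. If Additional file 1 says *serious*, the article contradicts it. If it says *severe*, the conflict with the governance section is in the procedures too.

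Three stronger readings are tempting, and the documents do not support them:

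- **That serious events of lower intensity will go unreported.** The governance commitment and the unseen procedures may well secure their reporting.
- **That the trial's safety record will be incomplete.** The trigger governs onward notification, not capture. Events still reach the principal investigator within 24 hours. Table 3 schedules adverse events at the visits after baseline and serious adverse events at the 6-month call.
- **That a severe but non-serious skin reaction will go to the ethics committee and regulator.** Side effects beyond mild have their own route: "Any reaction beyond that will be classified as potentially moderate or severe and will be reported to and discussed with the principal investigator". Applying the trigger to them takes the sentence out of its own sequence.

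**Conclusion.** The finding holds as an internal inconsistency. The only onward-reporting trigger stated in the article uses severity. Read literally, it leaves out serious events of mild or moderate intensity, and so it conflicts with the commitment under Ethics and Research Governance. This rests on taking *severe* in the sense that the same section gives it. An innocent slip remains plausible.

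The size cannot be put in events. A reader might multiply the serious-event rate quoted in the review of NRT safety by the 700 participants, but that rate is only given as fewer than 8% per arm. It is a share of participants rather than a count of events, and it comes from a different programme with 6 to 18 months of treatment. The share of serious events graded below severe appears nowhere in the article. Any count would therefore be assumption. The effect on the statistical analysis is nil. The point merits correction because it concerns safety oversight and costs almost nothing to put right.

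**What to change.** In the trigger sentence under Assessment of safety, replace *judged severe* with *judged serious*. State that onward reporting by the sponsor to the ethics committee and regulator follows the causality and expectedness assessments. Say that severity is recorded separately as an intensity grade. Then check the sentence against Ethics and Research Governance, Additional file 1 and the work instruction, so that all four carry one rule. If Additional file 1 already uses seriousness, only the article needs changing.

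The cost is one word, a clause and a cross-reference. The assessments needed are already required of the principal investigator, so there is no new data collection and no change to the sample size or analysis.
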